#### Infant outcomes

Infant birth weight and length: They will be measured using length and weight-measuring devices for infants (HLZ-20; Hualizheng, Tianjin, China) by professional obstetricians while infant is wearing light clothing. The scales for weight and length are calibrated at intervals of 10 g and 0.5 cm, respectively. Low birth weight for newborn infants is defined as a weight of < 2.5 kg, while macrosomia is defined as a weight of ≥4 kg. The growth of infant will be assessed according to the 2006 WHO Child Growth Standards [69].

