### Sample size calculation

For the calculation of sample size, the variable used is the incidence of new-onset hyperglycemia. Using the following formula, sample size is calculated:$$ {n}_1=\frac{\left(1+\raisebox{1ex}{$1$}\!\left/ \!\raisebox{-1ex}{$C$}\right.\right)\overline{p}\ \overline{q}{\left({U}_1-\raisebox{1ex}{$\alpha $}\!\left/ \!\raisebox{-1ex}{$2$}\right.+{U}_1-\beta \right)}^2}{{\left({P}_1-{P}_0\right)}^2} $$; *α* = 0.05, *β* = 0.20. Among these parameters, *p*_*1*_ = 20.9%, indicates the incidence of new-onset hyperglycemia among participants with insufficient fluid intake; *p*_*0*_ = 9.0%, means the incidence of new-onset hyperglycemia among participants with sufficient fluid intake; *c* = 4, indicates the ratio of pregnant women with water intake of > 0.5 L to pregnant women with water intake of < 0.5 L. These parameters were set based on the reference to the results of a related study [42]. A 10% dropout rate is taken into account to obtain the final sample size. For validity, 380 pregnant women will be needed.

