During childbirth and after childbirth: Before childbirth (One day before the expected date of delivery or one day before cesarean section), psychological state, sleep quality and time, physical activities and medication-use will be collected using corresponding questionnaires. On the day of childbirth, the mode of delivery will be recorded, pregnancy complications and other complications during childbirth will be assessed and diagnosed by professional obstetricians. Infant birth weight will be measured and health state will be assessed. Breastfeeding time and the crying behavior of infants before and after breast-feeding will be recorded. At 42 days after childbirth, maternal weight retention will be measured and calculated. Secretion of breast milk and mode of infant feeding will be consulted and infant growth will be assessed. Flow-process diagram of the study was shown in Fig. 2.

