### Data entry and statistical analysis

*Data entry*: All data will be documented twice by two trained researchers using the software of Epi Data 3.1 to ensure the accuracy of data.

*Statistical analysis*: SAS 9.2 (SAS Institute Inc., Cary, NC, USA) will be used. A mixed model of repeated-measures (ANOVA) will be used to analyze the differences of outcomes among participants with different hydration state. Multi-logistic regression analysis will be used to investigate the influencing factors related to maternal health and infant outcomes, such as fluid intake, hydration state, urine osmolality, concentration of copeptin and other indicators. The level of significance will be set at 0.05 (*p* < 0.05, 2-tailed) with 95% confidence intervals (95% CI).

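### Birth weight is taken with the infant lightly clothed and then cut at 2.5 kg and 4 kg with no stated correction; unless the clothing is removed from the reading, low birth weight can only be undercounted and macrosomia overcounted (minor).

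*Protocol article*

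**What the plan says.** All of this is in the protocol article.

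- **Infant outcomes:** birth weight and length are measured "by professional obstetricians while infant is wearing light clothing".
- **Same section, cut-offs:** "Low birth weight for newborn infants is defined as a weight of < 2.5 kg", and "macrosomia is defined as a weight of ≥4 kg".
- **Same section, instrument:** "The scales for weight and length are calibrated at intervals of 10 g and 0.5 cm, respectively".
- **Same section, growth:** "The growth of infant will be assessed according to the 2006 WHO Child Growth Standards".
- **Study procedure,** among the day-of-childbirth steps: "Infant birth weight will be measured and health state will be assessed". It does not mention clothing.
- **Sample size calculation:** "For validity, 380 pregnant women will be needed". This number already allows for 10% dropout and is based on new-onset hyperglycemia, not on infant weight.

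The article nowhere says that the clothing is weighed, tared or subtracted, or that a separate unclothed weight is taken.

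**The concern.** The article does not leave the weighing condition open. It specifies clothing, and then applies thresholds that are absolute values of the infant's own weight. A clothed reading is the infant's weight plus a positive quantity, so the error has one direction.

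Low birth weight and macrosomia are both classified from this reading. The Background cites work linking insufficient fluid intake to low birth weight, the statistical section plans logistic regression for infant outcomes, and the study aims to supply reference data. If the reading is gross, the reported rate of low birth weight is too low and that of macrosomia too high. Some infants near each cut are put in the wrong class, and any birth weight set against the growth standards is shifted upward.

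**Working it through.** **Plan's own figure.** The article states no expected birth weight and no rate of low birth weight or macrosomia, so there is nothing to reproduce on this point. The planned 380 serves only as a denominator. Since it includes 10% dropout, the births to count are about 380 × 0.90 = 342.

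**Direction (no assumption about the distribution).** Let W be the true weight and c > 0 the uncorrected clothing weight, so the recorded weight is W + c.

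- Recorded low birth weight: W + c < 2500 g, that is W < 2500 − c. This is a subset of W < 2500.
- Recorded macrosomia: W + c ≥ 4000 g, that is W ≥ 4000 − c. This contains W ≥ 4000.

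So the first count cannot rise and the second cannot fall.

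**Size (assumed inputs).** The article gives neither a clothing weight nor a birth-weight distribution. Assume W is Normal with mean 3200 g and SD 430 g, and take c = 0, 20, 50 and 100 g. Then, with Φ the standard normal distribution function:

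- P(low) = Φ((2500 − c − 3200)/430)
- P(macrosomia) = 1 − Φ((4000 − c − 3200)/430)

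| c | z at 2.5 kg | z at 4 kg | Low birth weight | Macrosomia | Infants of 342 (low / macrosomia) |
|---|---|---|---|---|---|
| 0 g | −1.628 | 1.860 | 5.18% | 3.14% | 17.7 / 10.7 |
| 20 g | −1.674 | 1.814 | 4.70% | 3.48% | 16.1 / 11.9 |
| 50 g | −1.744 | 1.744 | 4.06% | 4.06% | 13.9 / 13.9 |
| 100 g | −1.860 | 1.628 | 3.14% | 5.18% | 10.7 / 17.7 |

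Between 0 and 20 g the change is between one and two infants in each class. Between 0 and 100 g it is about seven.

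**Sensitivity to the assumed distribution.** Over means of 3100 to 3300 g and SDs of 400 to 500 g, the relative changes are:

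| c | Low birth weight | Macrosomia |
|---|---|---|
| 20 g | about −7 to −11% | about +8 to +14% |
| 50 g | about −16 to −26% | about +20 to +37% |
| 100 g | about −30 to −46% | about +43 to +86% |

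**Scale graduation.** Rounding to 10 g is symmetric and at most 5 g. Even if all of it acted as a one-way 5 g shift, low birth weight would go from 5.18% to 5.06% and macrosomia from 3.14% to 3.22%, about 2 to 3% in relative terms.

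**The case against.** The strongest reply is that the article does not say whether the recorded weight is gross or net. Taring is a procedural detail that a condensed article may leave to a site manual, so undercounting is not established as fact. This stands as a condition on the conclusion. It does not remove the point, because the article states the clothed condition and the cuts together, and followed as written they give a gross weight.

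Second, the study is about associations. Nothing in the article suggests that infant clothing depends on maternal hydration. A common offset cancels in differences of mean weight, and for the binary outcomes it acts like slightly moved cuts applied to every group. This also stands: what remains is distorted absolute rates, some misclassification near the cuts, and a shift against the growth standards.

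Third, the study calls itself preliminary and exploratory, and infant weight is one of many outcomes and not the basis of the sample size. That is fair and keeps the severity low.

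A reader might also infer more than the text supports:

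- *That some 40% of low-birth-weight cases will be lost.* That is the 100 g row under assumed inputs. The text says light clothing and the site is tropical, so 20 g belongs in the range as much as 100 g.
- *That the 10 g scale causes the error.* It does not, as the rounding check shows.
- *That infant weight gain to day 42 is wrong.* The clothing statement covers birth weight and length only; how infants are dressed at day 42 is not stated.
- *That the hydration comparison is biased.* Nothing in the article shows the offset to differ between groups.

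**Conclusion.** The point holds in conditional form, as a minor one. If the clothing weight is not removed, the stated procedure makes every birth weight too high, and the direction of both classification errors follows without further assumption. The size is not in the article. With Normal(3200 g, 430 g) and 342 births, it runs from between one and two infants per class at 20 g to about seven per class at 100 g (about 18 low-birth-weight and 11 macrosomic infants becoming about 11 and 18). These figures rest on the assumed distribution, the assumed clothing weights and the absence of a correction. The sample size is unaffected.

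**What to change.** In Infant outcomes, replace the clothed weighing by one sentence: infants are weighed unclothed, or the clothing is tared or weighed and subtracted, and net weight is recorded. State that the 2.5 kg and 4 kg cuts and the growth standards are applied to net weight. If the site already tares, say so.

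This costs one line in the measurement procedure and no added visit, staff or equipment. For infants already weighed clothed, record the usual weight of the clothing used and report a sensitivity analysis of both classifications with that weight subtracted.

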### Temperature and humidity of the environment

The temperature and humidity will be recorded according to the report of China Meteorological Administration at 9:00 AM and 3:00 PM each day.

### Confidentiality and withdrawal

The information confidential of the participants will be kept carefully in the whole process of study. During and after the trial, the names of participants will be replaced as study ID. Participants can withdraw from the trial freely as they wish. In case of adverse events, an emergency physician will be assigned to deal with them in time.

### Data entry and statistical analysis

*Data entry*: All data will be documented twice by two trained researchers using the software of Epi Data 3.1 to ensure the accuracy of data.

*Statistical analysis*: SAS 9.2 (SAS Institute Inc., Cary, NC, USA) will be used. A mixed model of repeated-measures (ANOVA) will be used to analyze the differences of outcomes among participants with different hydration state. Multi-logistic regression analysis will be used to investigate the influencing factors related to maternal health and infant outcomes, such as fluid intake, hydration state, urine osmolality, concentration of copeptin and other indicators. The level of significance will be set at 0.05 (*p* < 0.05, 2-tailed) with 95% confidence intervals (95% CI).

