### Definition of hydration

Hydration state is determined by the balance between water inputs and outputs and judged by the standard of urine osmolality. Dehydration is judged as urine osmolality of > 800 mOsm/kg, and it occurs when water inputs is insufficient to replace water outputs [44]. Middle hydration state is judged as urine osmolality between 500 and 800 mOsm/kg [45]. Optimal hydration state is judged as urine osmolality of ≤500 mOsm/kg [45].

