#### Pregnancy complications, other diseases or symptoms and maternal outcomes

Gestational hypertension: Blood pressure and will be measured twice by obstetricians to the nearest 2 mmHg with the desktop mercury sphygmomanometer (Yuwell, Danyang, Jiangsu, China). Two measurements will be taken after 2-min intervals. Hypertension of pregnancy will be defined as systolic blood pressure of > 140/90 mmHg and/or diastolic blood pressure of ≥90 mmHg sustained on two measurements.

Gestational diabetes mellitus (GDM): Blood glucose will be determined with elbow venous blood using an osmotic pressure molar concentration meter (SMC 30C; Tianhe, Tianjin, China) by laboratory physicians. GDM will be diagnosed based on the results of the 100-g, 3-h oral glucose tolerance test (OGTT) by obstetricians. According to the recommendations of the Committee on Obstetric Practice, a definite diagnosis is made if two or more thresholds be met or exceeded. The threshold of fasting blood glucose is as follows:5.3 mmol/L, 10.0 mmol/L for blood glucose of 1 h, 8.6 mmol/L for blood glucose of 2 h and 7.8 for blood glucose of 3 h [62].

Preeclampsia or eclampsia: Urine protein will be assessed using an automatic biochemical analyzer (Cobas C501; Roche; Basel, Switzerland) by laboratory physicians. Preeclampsia will be diagnosed at ≥20 weeks’ gestation along with new-onset gestational hypertension and new-onset proteinuria [63]. Eclampsia will be defined as the development of convulsions and/or unexplained coma during or after pregnancy with symptoms of preeclampsia, which will be diagnosed by obstetricians [64].

Anemia: Hemoglobin of elbow venous blood will be tested using automatic routine blood test device (MC-600, Kubeier, Shenzhen, China) by laboratory physicians. Anemia will be defined as < hemoglobin 110 g/L.

Oligohydramnios: Amniotic fluid will be measured using ultrasonography by professional medical technicians. Oligohydramnios is diagnosed by an amniotic fluid index (AFI) of < 5 cm or maximum amniotic fluid pool depth of < 2 cm [65].

Urinary tract infection: The diagnostic criteria is based on symptoms or laboratory confirmation including white blood cells and bacteria in urine by obstetricians. Routine urine test will be conducted using an automatic biochemical analyzer (Cobas C501; Roche; Basel, Switzerland) by laboratory obstetrician.

Spontaneous abortion: It will be recorded by obstetricians.

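### The only model named for intake, osmolality and copeptin is logistic, which can use birth weight and amniotic fluid index only as categories; a linear model should be added for these two measures

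*Protocol article*

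**What the plan says.** The section *Data entry and statistical analysis* of the protocol article names two methods.

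- For hydration classes: "A mixed model of repeated-measures (ANOVA) will be used to analyze the differences of outcomes among participants with different hydration state". *Definition of hydration* forms three classes by cutting urine osmolality at 500 and 800 mOsm/kg; for example, "Dehydration is judged as urine osmolality of > 800 mOsm/kg".
- For the wider set of exposures: "Multi-logistic regression analysis will be used to investigate the influencing factors related to maternal health and infant outcomes", with the factors listed as "such as fluid intake, hydration state, urine osmolality, concentration of copeptin and other indicators".

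No linear regression is named.

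*Infant outcomes* has birth weight read on a scale with 10 g steps and then sets two cuts: "Low birth weight for newborn infants is defined as a weight of < 2.5 kg, while macrosomia is defined as a weight of ≥4 kg". In the section on pregnancy complications, amniotic fluid is measured by ultrasound and has one category: "Oligohydramnios is diagnosed by an amniotic fluid index (AFI) of < 5 cm or maximum amniotic fluid pool depth of < 2 cm". Table 3 lists the infant outcome simply as infant weight. The Discussion names age, BMI, physiological state, sleep quality, food intake and physical activity as covariates.

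**The concern.** A logistic model, whether multivariable or multinomial, needs a categorical outcome. For birth weight and amniotic fluid index, the clinical cuts are the only categories supplied. In healthy women aged 21 to 35, such categories are likely to hold few events, although the protocol gives no rates. Cutting a measured variable far out in its tail discards most of the information about a shift in its mean.

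The association with maternal and infant outcomes is one of three stated objectives, and the authors want the results to inform intake recommendations. Part of the rationale in the Background is on the measured scale: it cites effects of total body water on birth weight, and an amniotic fluid index that rose by about 16% with extra water against about 8% without. If a shift of that kind is tested only through the cut, a real association has a materially higher chance of being reported as absent.

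**Working it through.** **Inputs from the protocol.** N = 380, 10% dropout, ratio c = 4, p1 = 20.9%, p0 = 9.0%, two-sided alpha 0.05, beta 0.20. Evaluable women: 380 × 0.9 = 342, which splits 1:4 into 68 and 274.

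**The plan's own sample size first.** With the weighted mean p̄ = (0.209 + 4 × 0.09)/5 = 0.1138:

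n1 = (1 + 1/4) × 0.1138 × 0.8862 × (1.960 + 0.842)² / (0.119)² = 69.9, so 70. The total is 5 × 70 = 350, and 350/0.9 = 389 (or 350 × 1.1 = 385). The stated 380 is reproduced within 3%.

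**Assumptions.** The protocol gives no SD or incidence for birth weight or amniotic fluid index. I assume a normal outcome, a pure shift in location, and a reference rate of low birth weight of 3%, 5% or 8%. For the size of the shift I use 0.30 SD, 0.40 SD and the normal-scale equivalent of the plan's hyperglycemia effect: Φ⁻¹(0.209) − Φ⁻¹(0.090) = −0.810 + 1.341 = 0.531 SD. That last value is borrowed as a yardstick; it is not evidence about birth weight.

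**Formulas.**
- Cut outcome: rate in the smaller group q = Φ(Φ⁻¹(p) + d); power = Φ((|q − p| − 1.960 × SE0)/SE1), where SE0 uses the pooled rate and SE1 the separate rates.
- Measured outcome: two-sample t-test with noncentrality d/√(1/68 + 1/274).

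**Example.** For p = 5% and d = 0.40, q = 10.7%, SE0 = 0.0325 and SE1 = 0.0397, so power is 43%. The t-test has noncentrality 2.95 and power 84%.

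| Shift (SD) | Cut, 3% | Cut, 5% | Cut, 8% | Measured scale |
|---|---|---|---|---|
| 0.53 | 56% | 65% | 73% | 97% |
| 0.40 | 36% | 43% | 50% | 84% |
| 0.30 | 23% | 27% | 31% | 60% |

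The loss runs from about 25 points (0.53 SD, 8%) to about 47 points (0.40 SD, 3%). Expected low-birth-weight events run from about 12 (274 × 0.03 + 68 × 0.057) to about 35 (274 × 0.08 + 68 × 0.191).

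**Continuous exposure.** The effect is set so that linear regression has 80% power with 342 women: r = (1.960 + 0.842)/√342 = 0.151. In 3,000 simulated data sets per scenario:

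| Method | Power |
|---|---|
| Linear regression on the measured outcome | about 80% |
| ANOVA of the measured outcome by three exposure classes (assumed 40/35/25 split) | about 60% |
| Logistic regression on a cut with 3 / 5 / 8 / 10% incidence | 19 / 26 / 32 / 37% |

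The asymptotic relative efficiency φ(z_p)²/(p(1 − p)) points the same way: at p = 5% it is 0.1031²/0.0475 = 0.22, like using 77 of the 342 women.

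The two-group calculation is for low birth weight. No such figure was worked for amniotic fluid index or macrosomia.

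**The case against.** The strongest counter-case has four parts.

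1. *A reader might infer that birth weight and amniotic fluid index will be analysed only as rare yes/no cuts.* No section says so. Defining low birth weight does not commit the plan to discarding weight in kg, and Table 3 lists infant weight. This objection stands. What remains is that the one model named for intake, continuous osmolality and copeptin has no use for the measured values.

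2. *A method for measured outcomes is already named.* This also stands in part. With one record per woman the mixed model reduces to an ordinary ANOVA, and nothing says that the amniotic fluid index is measured only once. But the method is named for hydration classes alone, its repeated-measures form does not suit a single birth weight, and grouping the exposure has its own cost (about 60% against 80%).

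3. *A reader might infer that most of the power is lost.* That is too strong as a general statement. In the nine two-group scenarios, more than half of the power is lost in three; at 0.53 SD and an 8% rate the loss is about a quarter. The rates are assumed and the 0.53 SD is borrowed from hyperglycemia.

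4. *The cuts have clinical standing, and this is a condensed article on an exploratory study.* The oligohydramnios criterion carries a citation, and the Background also reports low birth weight as a category linked to low fluid intake. That is a reason to keep the categories as results. A model for every outcome could be left to a fuller document, but the article does name a model for this purpose, and that model does not suit these two measures.

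**Conclusion.** The point holds in limited form. The named regression is a poor choice for birth weight and amniotic fluid index, and the only other named method does not cover intake, copeptin or continuous osmolality. If low birth weight as cut is what gets tested, the loss is about 25 to 47 points of power under an assumed 3-8% reference rate, a 1:4 split of 342 women and shifts of 0.3 to 0.53 SD. For a continuous exposure, power falls from 80% to about 25% with logistic regression on a 5% cut. These sizes rest on normality, a pure location shift and incidences that the protocol does not give. The documents do not support saying that the measured values will certainly go unused. The change should be made, but this is a weakness in the analysis wording and does not invalidate the design.

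**What to change.** In *Data entry and statistical analysis*, add a sentence to this effect: birth weight (kg) and amniotic fluid index (cm) will be analysed mainly by linear regression, or by a linear mixed model where the measure is repeated, on fluid intake, urine osmolality, hydration state and copeptin, adjusted for the covariates listed in the Discussion; the mean difference or slope will be reported with its 95% CI.

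Keep logistic regression for categorical outcomes and diagnoses. Report low birth weight, macrosomia and oligohydramnios alongside as secondary, clinically readable results.

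The cost is wording only: the measurements are already planned, and no new visits or participants are needed. The small downside is that a mean difference is less immediately clinical than a rate, which the secondary results offset.

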## Discussion

Pregnant women may need more fluid intake due to physiological changes in the mother and for fetal growth. Thus, the risk of being dehydration for pregnant women, due to insufficient fluid intake, is relatively high. However, surveys on fluid intake among pregnant women are scarce. Optimal hydration is essential for maintaining health. For pregnant women, the endocrine system shows considerable changes during pregnancy, which may affect water metabolism and balance and thus, hydration state. However, the importance of water and hydration, especially among pregnant women, is often neglected, and more research is required. In the present prospective cohort study, we will evaluate the fluid intake and hydration status of pregnant women and investigate the associations of fluid intake and hydration with pregnancy complications and maternal/infant outcomes.

The most considerable challenges in this study is the following up of participants and quality control. Important protocol modifications will be discussed and determined by the researcher group, and will be communicated to investigators, trial participants and other relevant parties by e-mail immediately. In the study, participants will be followed up from the first trimester of pregnancy to 42 days after childbirth. To increase the rate of follow up, effective and convenient methods of communication between participants and researchers will be established, including telephone call, home visits, e-mail, WeChat, short message and so on. The content and purpose of the study will be clearly clarified to establish a relationship of trust and raise awareness of participants concerning the importance of the study. In this study, many methods will also be used to ensure the quality control. The requirements for participants will be fully explained. Participants will also be trained to be familiarized with the content of related questionnaires and study requirements. If a participant failed to follow the requirements, her data will not be included in this study and the reason for dropout will also be recorded. Researchers will be trained on the procedure of this trial, the content of the questionnaires and the technology-related laboratory tests. Some indicators such as height, weight, and blood pressure will be measured twice for accuracy, such as height, weight and blood pressure. Food models and photographic models will be provided to help participants fill the questionnaire related to food and fluid intake after training to enhance estimation accuracy. Physiological indexes, such as blood and urine indicators, will be tested immediately after collection, in order to ensure the accuracy, and will be tested by laboratory physicians with the minimum 5 years of clinical experience to ensure accuracy. Trial conduction will be audited by a competent authority in the hospital every day, and the process will be independent from investigators and the sponsor. All the questionnaires will be regularly checked and stored for researcher rechecks. A data monitoring committee (DMC) is established and is comprised by six members (three clinicians, one statistician, one ethicist and one nutritionists), who are independent of the sponsor and competing interests. DMC will review the procedure and data of the study for once a week. The six members will evaluate the safety concerns and benefits to decide that if the study should be continued or terminated. They will also examine the quality of the data, supervise the quality control, record the follow-up process and supervise the process of data entry and analysis. Four hydration and fluid intake related projects has been completed in China by our team; these provided an authoritative questionnaire and technical supports for the study.

There are both strengths and weaknesses for the design of the present study. Referring to strengths, first, to eliminate the potential confounding factors as much as possible, age, BMI, physiological state, sleep quality, food intake and physical activity will be evaluated and included as covariates in the statistical analyses. Second, fluid intake is dependent on environmental factors, such as temperature and humidity. The conduction of this study will be in Hainan, which is an area with a tropical monsoon climate. Thus, temperature and humidity will be recorded clearly to actualize the comparability among different studies in China and with those in other countries. Third, hydration state will be evaluated in many indicators, not only including urine osmolality, but also including body compositions (ICF and ECF), copeptin, fluid intake and blood osmolality. Fourth, water intake from food will be assessed in order to calculate total water intake. Fifthly, the prospective cohort design can avoid recall bias and improve the accuracy of the results. In terms of weakness, the mechanism about the associations of hydration with pregnancy complications, maternal and infant outcomes will not be studied comprehensively. In this study, only the endocrine mechanisms related to hydration and pregnancy will be explored. An observational study will elucidate the associations but is not necessary for the development of recommendations unless confounding factors are carefully controlled.

In summary, it is the first time to assess water intake and hydration stare among pregnant women, and it is the first time to investigate the associations of hydration with pregnancy complications, maternal and infant outcomes in China. Our results can provide some scientific reference data for updating the recommendations on fluid take for pregnant women and valuable evidence on the importance of hydration on maternal health during pregnancy. The results may also raise awareness on the importance of adequate fluid intake and optimal hydration in Chinese residents, especially pregnant women. More multicenter studies with larger sample sizes are required for the development of clinical guidelines and recommendations. The final goal is to develop water intake–related interventions to improve maternal health and birth outcomes.

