## Methods/design

### Study hypotheses

One hypothesis is that a certain proportion of pregnant women have insufficient water intake and have risk of being in dehydration state. Another hypothesis is that dehydration state induced by insufficient water intake affects maternal health and birth outcomes.

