**Fig. 2 Fig2:**
[figure not shown]
Flow-process diagram of the study

If participants in this study requires hospitalization for any reason or receives intravenous fluid, or develops vomiting or diarrhea or fever or respiratory tract infections during pregnancy, the occurrence time, duration and treatment measures of these incidents will be recorded in detail. The time for recording fluid intake, food intake and other indicators will be exchanged within the allowable range of corresponding research phase to stagger the occurrence and duration of these situations.

The schedule of enrolment, data collections and assessments are shown in Table 2.

**Table 2 Tab2:** The schedule of enrolment, interventions, and assessments

Timepoint	15 April 2019	15 April 2019–30 September 2020	1 Octorber 2020
Enrolment:			
Eligibility screen	√	√	
Informed consent	√	√	
Collection of basic information	√	√	
Assessments of related indicators and outcomes during pregnancy and childbirth	√	√	
Close-out			√

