### Assessment of indicators and outcomes

#### Fluid intake

After standardized training by researchers, daily fluid intake of participants will be collected using a 7-day 24-h fluid intake record by themselves for correct use of such records. The amount of fluid intake for each time in seven consecutive days will be measured using a customized cup, and the nearest of cup scale is10 mL. This method has been proved to be reliable in many water intake-related studies [21, 46, 47]. The volume, type, time and place of water intake will also be recorded by participants. All types of fluid intake will be recorded in detail including plain water, bottled water, tea, sugar-sweetened beverages, and so on. The record will be photographed and sent by participants to the investigators using a mobile phone, and will be reviewed by investigators every day to ensure the accuracy and the integrity of the records.

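### Dropping all data of women who do not follow the requirements can bias the prevalence estimates and the associations, by an amount and in a direction the protocol does not determine

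*Protocol article*

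**What the plan says.** The quality-control text of the Discussion states: "If a participant failed to follow the requirements, her data will not be included in this study". It adds that "the reason for dropout will also be recorded". That sentence neither lists the requirements nor says how much failure triggers exclusion.

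Other sections bear on the rule:

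- Study hypotheses: "One hypothesis is that a certain proportion of pregnant women have insufficient water intake". The first aim is therefore a proportion. The second hypothesis concerns the effect of dehydration on maternal health and birth outcomes.
- Fluid intake: "daily fluid intake of participants will be collected using a 7-day 24-h fluid intake record by themselves". Investigators review photographs of the record every day. Table 3 schedules fluid intake, diet and other factors in three pregnancy phases and around childbirth.
- Study procedure, text after Fig. 2: for hospitalisation, intravenous fluid, vomiting, diarrhoea, fever or respiratory infection, "The time for recording fluid intake, food intake and other indicators will be exchanged within the allowable range of corresponding research phase".
- Data entry and statistical analysis: "A mixed model of repeated-measures (ANOVA) will be used to analyze the differences of outcomes among participants with different hydration state". Logistic regression is planned as well.
- Sample size calculation: "A 10% dropout rate is taken into account to obtain the final sample size".

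**The concern.** Adherence is behaviour after enrolment, while the exposure is already present and outcomes are accruing. A rule that removes a woman entirely because of that behaviour selects the analysed cohort on something that may be related to intake, to complications, or to both.

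Three things are at stake. The proportion with insufficient intake or dehydration is biased if adherence depends on intake alone. The association with complications is biased if exclusion depends jointly on hydration and outcome. Valid visits and known outcomes are also thrown away, although the planned repeated-measures mixed model can use women with some visits missing. The 10% allowance makes up for lost numbers. It does nothing about who is lost.

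Because no threshold is given, exclusion is also left to judgement after data have been seen.

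**Working it through.** **Inputs from Sample size calculation.** p1 = 20.9% (insufficient fluid intake), p0 = 9.0% (sufficient fluid intake), c = 4 sufficient women per insufficient woman, α = 0.05 (two-sided per the statistical analysis section), β = 0.20, dropout 10%, N = 380. These rates are by fluid intake, not by urine osmolality, so the groups below are called low-intake and other.

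**The plan's own figure.** Weighted mean risk = (0.209 + 4 × 0.090)/5 = 0.1138. Then n1 = (1 + 1/4) × 0.1138 × 0.8862 × (1.960 + 0.842)² / 0.119² = 69.9. Rounded up, this is 70 low-intake women and 350 in total. Adding 10% gives 350/0.9 = 389 or 350 × 1.1 = 385. The stated 380 is within 3% of either and is accepted here.

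**Baseline after a random 10% loss.** 380 × 0.9 = 342, about 68 low-intake and 274 other. The risk difference is 11.9 points. The odds ratio is (0.209/0.791)/(0.090/0.910) = 2.67. Exact power of the two-sided pooled test, by summing over both binomial distributions, is 74.6%.

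**Effect on the prevalence.** With c = 4 the true low-intake share is 1/5 = 20%. Assume 70% of low-intake and 95% of other women are kept. The share kept is 0.20 × 0.70 + 0.80 × 0.95 = 0.90, so only 10% are lost. The observed share is 0.14/0.90 = 15.6%.

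**Effect on the association, one assumed pattern.** Exclude 10% generally, but a fraction a of low-intake women who have the complication:

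observed p1 = 0.209(1 − a) / [0.209(1 − a) + 0.791 × 0.9]

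The odds ratio is 2.67 × (1 − a)/0.9. Power is at 68 vs 274.

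| a | observed p1 | risk difference (points) | odds ratio | exact power | total excluded |
|---|---|---|---|---|---|
| 0.10 | 20.9% | 11.9 | 2.67 | 74.6% | 10.0% |
| 0.20 | 19.0% | 10.0 | 2.37 | 62.5% | 10.4% |
| 0.25 | 18.0% | 9.0 | 2.23 | 55.4% | 10.6% |
| 0.30 | 17.0% | 8.0 | 2.08 | 47.7% | 10.8% |

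Total loss stays close to the planned 10%, so the dropout count would not reveal the problem.

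**Other assumed patterns.**

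- Exclusion at random, by exposure only, by outcome only, or by both acting multiplicatively: the odds ratio stays at 2.67.
- 20–30% of women with the complication excluded in both groups, 10% of the rest: observed p0 = 8.1–7.1%, risk difference 10.9–9.9 points, odds ratio 2.67, exact power about 71–67%.
- 20–30% of the other (sufficient-intake) women with the complication excluded, 10% of everyone else: risk difference 12.8–13.8 points, odds ratio 3.0–3.4. The distortion now runs upwards.

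All retention and exclusion fractions are assumptions. The protocol gives no expected rate of non-adherence and no information on who fails.

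**The case against.** A reader might infer that the rule does remove women for reasons tied to hydration and complications, and so does bias the associations. The protocol does not support that. It does not say who will fail the requirements or how many will.

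It also contains measures against the most obvious route. Recording is moved within the phase window around hospitalisation, vomiting, fever and similar events, so a short illness need not cause failure. Participants are trained, fluid records are checked daily, contact is kept up by calls, home visits and messages, and reasons are recorded. The downward bias above comes from one chosen pattern. Others leave the odds ratio, which the logistic regression would estimate, untouched or raise it. The 75% starting power already reflects the planned 10% loss and is not an effect of the rule.

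It can also be said that the study describes itself as preliminary and exploratory, that this is one sentence in a condensed article, and that analysis sets and missing-data methods usually belong in an analysis plan that is not shown.

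Most of this stands and limits the claim to a possibility. It does not remove the rule. Rescheduling works only inside the window and does not cover low motivation, anxiety or low intake as reasons for failing. Recording reasons documents an exclusion without undoing it. And the sentence is not a missing detail: it commits the study to leaving out the whole participant.

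**Conclusion.** The point holds as a risk of bias. The protocol fixes a whole-participant exclusion after enrolment, with no threshold, that can discard valid visits and known outcomes.

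The prevalence estimate is the more exposed, since it needs only a relation between adherence and intake. Bias in the odds ratio needs exclusion that depends jointly, and not merely multiplicatively, on hydration and outcome. The figures shown illustrate what a loss near the planned 10% could do under assumed retention. Neither the size nor the direction of any actual bias can be determined from the document. Should be fixed, before analysis.

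**What to change.** Replace the sentence in the Discussion so that:

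- every enrolled woman is kept with all data collected up to withdrawal;
- only the invalid item or visit, such as an incomplete 7-day record, is set to missing, with the requirements and the threshold for invalidity defined;
- the main analysis uses all women with at least one valid exposure measurement and an observed outcome;
- the fully compliant subset serves only as a sensitivity analysis;
- reasons for non-adherence are reported by hydration state and outcome.

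The cost is a short change of text, some extra analysis, and slightly noisier exposure data from partial compliers.
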